## Abstract

**Background:**

Delirium is a clinical condition characterised by acute and fluctuating deterioration of the cognitive state, generally secondary to an acute pathology. Delirium is associated with negative outcomes in older adults, such as longer hospitalisations, higher mortality, and short and medium-term institutionalisation. Randomised clinical trials have shown that delirium is preventable through non-pharmacological prevention measures, decreasing its incidence by 30–50%. These interventions include promoting physical activity, facilitating the use of glasses and hearing aids, cognitive stimulation, and providing frequent reorientation of time and space, among others. These measures are currently seldom applied in hospitals in Chile and around the world for reasons including the heavy workload of clinical staff, the lack of trained personnel, and in general the absence of a systematic implementation processes.

We developed a software called PREVEDEL, which includes non-pharmacological strategies such as cognitive stimulation, early mobilisation, orientation, and pain assessment. We propose a randomised clinical trial to evaluate whether cognitive stimulation guided by PREVEDEL software prevents delirium status (full/subsyndromal delirium) in hospitalised older adults.

**Method:**

A randomised controlled trial, with parallel, multicentre groups. We will recruite patients 65 years or older who have been hospitalised for less than 48 h in the general ward or the intermediate care units of four hospitals in Santiago, Chile. The participants in the intervention group will use a tablet with cognitive stimulation software for delirium prevention for five continuous days versus the control group who will use the tablet without the software.

We will evaluate the incidence, duration, density of delirium, subsyndromal delirium with the Confusion Assessment Method, cognitive with the Montreal Cognitive Assessment, and functional status with the Functional Independence Measure at discharge. Moreover, we will evaluate the adherence to prevention measures, as well as demographic variables of interest.

**Discussion:**

The use of cognitive PREVEDEL software could increase and improve the implementation of non-pharmacological prevention measures for delirium in hospitalised older adults, thus reducing its incidence and contributing to patients and health professionals.

**Trial registration:**

NCT05108207 ClinicalTrials.gov. Registered 4 November 2021.

## Background

Delirium is a clinical condition characterised by acute cognitive impairment, of fluctuating course, generally secondary to an acute pathology, which appears after the interaction between predisposing factors and well-described precipitants. It is a very common condition in older adults, observed in 20–30% of patients hospitalised in a general ward, and up to 80% of those hospitalised in critical care units [1]. Delirium is associated with negative clinical outcomes which include longer hospitalisations, increased direct and indirect costs, functional impairment, greater risk of mortality, increased risk of institutionalisation, and deterioration of long-term cognitive status, among others [1–4].

Subsyndromal delirium is a milder state characterised by the presence of certain delirium symptoms but without meeting full diagnostic criteria thresholds, is also associated with poor posthospitalisation outcomes similar to those associated with delirium [5]. The reported frequency of subsyndromal delirium varies (7–50%) according to the definition applied and the clinical population studied. Its incidence in the general medicine ward is 17% [6].

Delirium in hospitalised older adults is preventable. In multiple randomised clinical trials, non‐pharmacological interventions to prevent delirium (nPPD), shown to reduce its incidence by 30–50% [7]. These interventions include promoting physical activity, facilitating the use of glasses and hearing aids, and providing frequent temporospatial orientation and cognitive stimulation, among others [8, 9]. Despite the high evidence supporting them, nPPD are poorly implemented in hospitals in Chile and around the world for several reasons, including the heavy workload of clinical staff, lack of trained personnel, and in general, the absence of systematic implementation processes [10, 11]. The professional who can more systematically promote cognitive stimulation at the hospital is the occupational therapist. It has been seen that delirium has been prevented in non-ventilated older adults who receive therapy twice a day [9]. However, considering the large number of hospitalised older adults and the number of interventions required for each patient, this alternative is sometimes not very accessible.

Before this clinical trial, local pilot studies have shown some progress in this area. It has been reported that the incorporation of software technology through a "PREVEDEL" tablet is feasible and can be implemented on a hospital level, with possible effects on decreasing delirium [12] and the implementation of nPPD following a theoretical model improves the adherence of health personnel [13].

We propose a multicentre randomised clinical trial to evaluate whether cognitive stimulation guided by PREVEDEL software prevents delirium in hospitalised older adults and whether it is a technology that can be used in others hospital centres. The principal aim is to compare the incidence of delirium and subsyndromal delirium in hospitalised older adults using cognitive stimulation guided by PREVEDEL software versus nPPD.

## Methods and design

### Study design

This will be a multi-centre, parallel-group, randomised controlled trial (RCT). CONSORT methodological recommendations will be used for reporting non-pharmacological trials, in addition to Templates for Intervention Description and Replication and Standard Protocol Items: Recommendations for Interventional Trials. This project was registered at ClinicalTrials.gov, the identifier is NCT05108207.

### Participants

The research is developed in four hospital centres of similar complexity located in Santiago, Chile. These are: Hospital Clínico de la Universidad de Chile (HCUCH), Hospital San Juan de Dios, Clínica Las Condes, and Hospital Santiago Oriente [name]. Two are public institutions and two are private institutions. Patients hospitalised in general wards (Geriatric and Internal Medicine Units) and Intermediate Care Units. The units serve older adults admitted for acute pathologies, in the intermediate care unit patients can receive non-invasive ventilation, high-flow nasal cannula, and low doses of vasopressors.

We will include patients 65 years or older, hospitalised less than 48 h prior in a general ward or the intermediate care unit of four participating centres. Patients with full or syndromal delirium (Confusion Assessment Method-[CAM] + or presence of one core element) history of dementia (Alzheimer’s Disease-AD8 greater than 2 points), and non-Spanish speaking patients will be excluded.

### Interventions

Patients will be randomised to one of the following groups: (i) the control group: will receive the standard delirium prevention measures outlined above, plus the use of a mobile device without delirium prevention software for five days (control group: nPPD package, without PREVEDEL) or (ii) the experimental group: will receive the standard delirium prevention measures, plus the use of a mobile device with PREVEDEL software for five days (experimental Group: nPPD package, with PREVEDEL).

A)Preparation of interventions to implement a programme of nPPD in the centres.

Three months before the start of the clinical trial, an intervention will be conducted in the internal medicine, geriatrics, and intermediate care unit services of the four participating centres to establish a homogeneous plan of nPPD and assess adherence. The implementation methodology in the first stage will follow the Consolidated Framework for Advancing Implementation Science model, used in a local pilot study [13]. The following actions are considered:

To assess healthcare personnel's knowledge and beliefs about delirium. The same questionnaire is used as in the previous pilot study of implementation in HCUCH [13].Define local leaders and roles. Leaders are designated according to interest and motivation to lead the implementation of the protocol in their unit with the aim of incorporating the proposed activities into the daily care routine. These leaders will have meetings for feedback and support.Delivery of study material.Approval of online course on delirium and nPPD.Assessment of adherence to four non-pharmacological prevention domains (12 indicators): Management of environment (visible clock, visible calendar and decrease physical restrictions) early mobilisation (indication of relative rest, encourage the patient to sit and stand), correction of sensory deficits (availability of glasses, hearing aids, and dentures when necessary), management of medications (decrease the use of benzodiazepines, anticholinergics, and metoclopramide when possible) [13]. The control and experimental groups will have four non-pharmacological prevention domains.Provide an informative diptych on delirium for the patients and families.

B)Use a mobile device. We will use an Alcatel OneTouch Pixi-3 10 tablet which will be delivered daily to each patient between 9:00 am and 8:00 pm, with nighttime pickup (8:00 pm to 09:00 am), so the patient can rest and to charge the device. On the first day, a previously trained health professional will deliver the tablet and train the patients in its use, taking 10–15 min. The day after the tablet is delivered, the same person will go to the patient's room to check if he or she has any questions or problems with its use. Both groups are advised to use the tablet three times a day, for at least ten minutes each time.

To evaluate patient adherence and how the tablet is used, both groups will have an application installed in their devices that will allow them to keep track of the duration of use and applications used.

C)The control group will receive the standard delirium prevention measures outlined above, plus the *use of a mobile device without delirium prevention software* for five days (Control Group: nPPD package, without PREVEDEL).D)The experimental group will receive the standard delirium prevention measures, plus the use of a mobile device with PREVEDEL software for five days (experimental Group: nPPD package, with PREVEDEL).E)The PREVEDEL software was designed and evaluated in a previous study in Chile. It proved to be highly accessible and feasible to improve access to nPPD in hospitalised older adults and showed its possible effect in decreasing the incidence of delirium [12].

To define the software content, a search was carried out in the literature of systematic reviews on non-pharmacological prevention of delirium. The data were reviewed, and the multidisciplinary team chose specific interventions based on their evidence and the feasibility of their incorporation into the software. A literature search was conducted to define the design characteristics of the software and to optimise accessibility for older adults. The data were reviewed, and the multidisciplinary team selected specific design features based on their clinical experience, the technical feasibility to be incorporated into the software, and the opinion of the older adults who participated in the software development.

The software developed was organised into several modules for easy access, which include:A)Desktop module: this is the first screen the user faces when the software is turned on. It continuously delivers information for temporal and spatial reorientation and allows access to other modules.B)The exercise module contains 12 physical activity videos guided by physical therapists, which can be easily performed by older adults. All exercises are focused on functional activities.C)Games module: includes eight cognitive activities to stimulate attention, memory, and executive function. Colloquial names were selected to improve accessibility. Two different categories of difficulty were considered, according to the patient's level of education based on the above data [14].D)The documentary module contains short videos intended to be a tool for cognitive stimulation, an entertainment activity during free time, and a tool to educate about delirium.E)Alert module: a series of pre-set alerts are displayed during the use of the software. These include the promotion of sensory support measures (glasses, hearing aids), assessment of pain level, and sleep recommendations, with a customisable frequency.F)Configuration module: allows software customisation. It is possible to configure patient data, including educational level, the use of sensory support, and restriction of patient movement if indicated. Access to this module can be password-protected. Healthcare personnel, especially nurses, can use this module to customise the software according to each patient's profile. For example, if the patient has an indication for absolute rest, it is possible to hide all physical activity videos, and if there is a ban on aerobic activity, only exercises with low metabolic demand are shown.G)Registration system. The software keeps a complete record of its use, including the total duration of use and the duration for each module. It also records the number of correct or incorrect answers for cognitive games.

### Outcomes

A)Primary outcome:

To evaluate the incidence of delirium and incidence of subsyndromal delirium by applying the CAM [15] twice daily during five days of hospitalisation.

The incidence of basal delirium will be determined before the software is implemented in a group of patients enrolled prospectively with the same inclusion/exclusion criteria and delirium assessment protocol.

B)Secondary outcomes:Duration of delirium (days) and density of delirium (incidence x duration) will be assessed with the CAM.Level of independence in basic activities of daily living on day 5, will be assessed using the Functional Independence Measure (FIM), this instrument evaluates independence in 18 activities of daily living (13 motor and five cognitive items). The scale has seven levels (1–7, from lower to higher levels of independence). The motor FIM score ranges from 13–91, cognitive FIM from 5–35 points, and total FIM from 18–26 points; higher scores indicate greater independence [16].Cognitive level on Day 5 assessed using the Montreal Cognitive Assessment. The test evaluates attention and concentration, executive functions-memory, language, visuoconstructional skills, conceptual thinking-calculations, and orientation. It has Chilean validation in the population over 60 years of age [17].Hospital stay (days).90-day mortality.Duration of device use will be compared using the internal device registration.Presence of sleep disorders and headache will be evaluated using a self-reporting instrument in both groups. The doctor in charge of the patient will be informed for management.Adherence to the nPPD programme will be evaluated in the four participating centres before and after training in prevention measures. Assessment of adherence to non-pharmacological prevention domains (12 indicators) will be conducted [13].

In addition, socio-demographic data and clinical information will be gathered including The reason for admission, the Acute Physiology and Chronic Health disease Classification System II score, the Sequential Organ Failure Assessment), and the Charlson Comorbidity Index.

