### Study sample

Local and literature data were evaluated to calculate the sample size [1, 13]. A delirium status prevalence of 20% is estimated in the control group and a decrease in prevalence to 8% in the intervention group is expected. In this way, with a power of 80%, and an alpha of 0.05 bilaterally, 147 patients will be enrolled in each group. If we add to this a 10% loss of follow-up, the overall sample size will be 320 patients (See flow chart in Fig. 1).

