### Analysis and statistical methods

The results will be analysed with the intention to treat. For the descriptive analysis of the variables, we will use the mean (standard deviation), median (25–75 percentile), or proportions as appropriate to the type and distribution of the data.

Analytical Statistics: For the primary outcome, a comparison of proportions between patients who develop delirium and subsyndromal delirium in both groups will be made, using Fisher's exact test, and as a measure of efficacy, an odds ratio with 95% confidence interval will be estimated. If there is any baseline variable that is not matched by the randomisation, efficacy analyses will be conducted using logistic regression with the main variable being the treatment, and the adjustment variables will be those that the randomisation would not have been able to match. Additionally, to compare the effect of the intervention over time, a time-to-event analysis will be performed using the Kaplan-Maier procedure and then the Cox regression model to adjust for baseline variables and the presence of the intervention. For the secondary outcomes, the Fisher's exact test or t-test will be used, as appropriate for the type and distribution of the data. Linear regression or multivariate logistics will also be performed, as appropriate, to evaluate the impact of the intervention, adjusting for the input covariates. A bilateral *p* < 0.05 significance level will be used for all analyses.

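### The primary outcome is two separate incidences in one section and one combined delirium status in others, and only the combined status carries the stated sample size and error rate

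*Protocol article*

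**What the plan says.** All places are in the protocol article.

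- **Outcomes, primary outcome:** "To evaluate the incidence of delirium and incidence of subsyndromal delirium by applying the CAM", with the CAM applied twice daily for five days. The word for incidence is repeated, once for each condition.
- **Abstract, Background:** the trial asks whether the software "prevents delirium status (full/subsyndromal delirium) in hospitalised older adults". This is one combined status.
- **Study sample:** "A delirium status prevalence of 20% is estimated in the control group" and "a decrease in prevalence to 8% in the intervention group is expected"; then "with a power of 80%, and an alpha of 0.05 bilaterally, 147 patients will be enrolled in each group". There is one pair of rates, and alpha is not split.
- **Background, last paragraph:** "The principal aim is to compare the incidence of delirium and subsyndromal delirium in hospitalised older adults". Pooled or separate is not said.
- **Analysis and statistical methods:** "a comparison of proportions between patients who develop delirium and subsyndromal delirium in both groups will be made", by Fisher's exact test with an odds ratio. This too can be read either way. The section ends by stating that a two-sided p < 0.05 "significance level will be used for all analyses".

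The article gives no alpha split, no testing order, no rule for which result decides success, and no rule for counting a patient who passes through both states.

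**The concern.** Which endpoint is primary is core protocol content, and here it is fixed in two incompatible ways. An analysis plan could choose one reading, but it would then contradict either the Outcomes section or the Abstract and Study sample section.

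Three things are at stake. First, if both incidences are tested at 0.05, there are two routes to a significant primary result, and three if the combined status is tested too. Second, the stated power was worked out for one comparison of one rate. Third, a separate subsyndromal comparison can be hard to read. The Background describes subsyndromal delirium as the milder state. If patients were classified by their worst state, moving some from full to subsyndromal delirium could raise subsyndromal incidence. The Kaplan-Meier and Cox analyses inherit the same undefined event.

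**Working it through.** **1. Reproduce the plan's figure.** Inputs from Study sample: p1 = 0.20, p2 = 0.08, mean 0.14, difference 0.12, two-sided alpha 0.05 (z = 1.960), power 80% (z = 0.842).

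Without continuity correction:
n0 = [1.960·√(2·0.14·0.86) + 0.842·√(0.20·0.80 + 0.08·0.92)]² / 0.12² = 130.1, so 131.

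With continuity correction:
n = (n0/4)·[1 + √(1 + 4/(n0·0.12))]² = (130.1/4)·[1 + √1.256]² = 146.3, so 147.

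The stated 147 per group is reproduced exactly, as a single comparison of the combined status with unsplit alpha.

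**2. False-positive rate with no effect.** Trials were simulated with 147 per arm, each patient falling in one of three classes (full, subsyndromal only, neither), and Fisher's exact test at two-sided 0.05. The article does not divide its 20% between the two conditions, so the control rates below are assumptions. The 20% plus 17% row is prompted by the ward figures in the Background.

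| Full / subsyndromal | Combined alone | Either component | Either component or combined |
|---|---|---|---|
| 10% / 10% | 3.6% | 6.5% | 8.2% |
| 12% / 8% | 3.6% | 6.2% | 8.0% |
| 5% / 15% | 3.6% | 5.7% | 7.3% |
| 15% / 5% | 3.6% | 5.7% | 7.3% |
| 20% / 17% | 3.7% | 6.9% | 8.8% |

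Repeat runs differ by about 0.1 percentage point, which gives the ranges 3.6-3.7%, 5.7-6.9% and 7.3-8.9%. A more lopsided split of 3% / 17% gives 5.3% and 6.6%.

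**3. Power at 147 per arm, exact Fisher, two-sided 0.05.** The article's relative reduction is kept: 0.08/0.20 = 0.4.

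| Control vs intervention | Power |
|---|---|
| 20% vs 8% (the combined status as sized) | 81.8% |
| 17% vs 6.8% | 74% |
| 15% vs 6% | 67% |
| 10% vs 4% | 44% |

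If the 20% is divided between two components, the smaller is at most 10%. Power rises with the control rate here, so the smaller component has at most 44%. No split gives both components 80%.

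**4. Cost of keeping two primaries.** With 0.025 for each, and even at the full 20% vs 8% contrast, the same continuity-corrected formula gives 174 per group. With 10% loss, 174/0.9 = 193.3, so 194 per group and 388 in total. Exact Fisher power at 147 falls from 81.8% to 72.6%.

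**The case against.** The combined reading is well supported. The Abstract defines the status, the Study sample section uses it, and 147 fits it exactly. On that reading there is one primary test and no inflation. This stands: the error rates above describe what follows if the Outcomes section is applied as worded, not what the trial will certainly do.

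Several stronger readings are tempting, and the documents do not support them.

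- **The error rate doubles to about 10%, or exceeds 14%.** Two or three independent tests at 0.05 give 9.75% and 14.3%, and uncorrected chi-square tests give roughly 9-12% for these outcomes. But the article specifies Fisher's exact test, which is conservative, and the three outcomes are correlated. The rise is roughly twofold, but from 3.6%, not from 5%.
- **All of this is false success.** The rates are two-sided. On the 10/10, 12/8 and 20/17 rates, a false result in favour of the software has probability 3.2-3.6% with two tests and 4.0-4.5% with three, against about 3.6%/2 = 1.8% for the combined status alone.
- **Neither component can have 80% power.** This depends on dividing the 20%. The Background puts full delirium alone at 20-30% in general wards. If full delirium ran at 20% vs 8%, its power would be 81.8%.
- **The two states are mutually exclusive, so benefit would appear as harm.** They exclude each other at one assessment, but over ten assessments a patient can pass through both. The reversal needs a worst-state rule that the article does not give, and more downgraded patients than prevented subsyndromal cases.

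Detailed counting rules and testing hierarchies can properly sit in a full protocol or analysis plan. That does not excuse two conflicting statements of the primary outcome in this article.

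**Conclusion.** The point holds: the article states its primary outcome in two incompatible ways, and nothing in it resolves the conflict. The sample size fits only the combined status tested once.

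If the two incidences were tested separately, the two-sided false-positive rate would be about 5.7-6.9%, or 7.3-8.9% with the combined status also allowed. That is a moderate excess over the nominal 5%. It assumes the control rates listed above, one class per patient, and Fisher's exact test at 147 per arm. Power for a component would be 44-74% at control rates of 10-17% with the same relative reduction; only the combined status has the planned 80%. The difficulty of reading a subsyndromal comparison is conditional on worst-state classification.

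Confidence is high for the inconsistency itself. The sizes are illustrative, because the article gives no split between full and subsyndromal delirium.

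**What to change.** In the Background aim, the Outcomes section and the analysis section, name one primary outcome: combined delirium status, full or subsyndromal, at any CAM over the five days. Test it once at two-sided 0.05. List full delirium and subsyndromal delirium separately as secondary outcomes, reported with confidence intervals. State how a patient who passes through both states is counted, and use the same combined event in the time-to-event analysis.

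This is a change of wording, and the sample size stays at 147 per group before loss. The only cost is giving up separate primary claims for the components. If the sponsor wants to keep both incidences as primary, the article needs an alpha split or a fixed testing order, and the trial must be sized again on stated component rates.

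### MoCA and FIM are set at day 5 in one section and at discharge in another; under the day-5 rule, patients who leave early, mainly those without delirium, may go unscored

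*Protocol article*

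**What the plan says.** In the protocol article, Outcomes (secondary outcomes) lists "Cognitive level on Day 5 assessed using the Montreal Cognitive Assessment" and, for the FIM, "Level of independence in basic activities of daily living on day 5". The Method paragraph of the Abstract puts the same assessments at discharge. The wording there is explicit for the FIM, and the natural reading carries it to the MoCA in the same sentence.

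Participants admits acute patients within 48 hours of hospitalisation and sets no minimum stay. Length of stay is itself a secondary outcome. The Background states: "Delirium is associated with negative clinical outcomes which include longer hospitalisations".

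Analysis and statistical methods declares an intention-to-treat analysis and says "For the secondary outcomes, the Fisher's exact test or t-test will be used", as suits the data, followed by covariate-adjusted regression. Study sample gives the planning rates: "A delirium status prevalence of 20% is estimated in the control group and a decrease in prevalence to 8% in the intervention group is expected".

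**The concern.** The two time points do not give the same data. A patient who goes home on day 3 has a score under the discharge rule and possibly none under the day-5 rule. By the article's own account delirium goes with longer stays, so early leavers would mainly be patients without delirium. If they are unscored, the patients left for comparison are richer in delirium than the randomised arms, and more so in the arm with more delirium. The contrast would then depart from the intention-to-treat comparison that the article states.

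A later analysis plan can choose how to treat missing scores, but it cannot recover a MoCA or FIM that was never taken. The timing therefore has to be settled before patients leave hospital.

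**Working it through.** **1. The two rules side by side**

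| Patient | Day-5 rule (Outcomes) | Discharge rule (Abstract) |
|---|---|---|
| Leaves before day 5 | may have no score | scored on leaving |
| Leaves on day 5 | scored on day 5 | scored on day 5 |
| Leaves after day 5 | scored on day 5 | scored later, at a time that depends on stay |
| Dies in hospital before day 5 | no score | no score |

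The rules agree on a score only for patients who leave on day 5.

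**2. The plan's own figure**

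Inputs from Study sample: 20% vs 8%, 80% power, two-sided alpha 0.05. The mean rate is 0.14.

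- Without continuity correction: n' = [1.96·√(2·0.14·0.86) + 0.8416·√(0.20·0.80 + 0.08·0.92)]² / 0.12² = 1.873 / 0.0144 ≈ 130.1, rounded up to 131.
- With continuity correction: n = (n'/4)·[1 + √(1 + 4/(n'·0.12))]² ≈ 146.3, rounded up to 147.

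This is the stated 147 per group, so 20% and 8% are the right planning rates to carry forward. The stated total of 320 gives 160 per arm.

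**3. Early discharge**

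Assumptions not in the documents: a share e of patients without delirium status leaves before day 5 and is unscored; patients with delirium status all stay; and the software acts on the MoCA only through delirium status. The delirious fraction among scored patients is

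p / [p + (1 − p)(1 − e)].

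The expected difference is the between-arm gap in this fraction times the MoCA deficit of a delirious patient. The deficit cancels from the ratio to the full-data gap of 0.20 − 0.08 = 0.12.

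| e | Control | Experimental | Gap | Gap / 0.12 |
|---|---|---|---|---|
| 0.10 | 0.20/0.920 = 0.217 | 0.08/0.908 = 0.088 | 0.129 | 1.08 |
| 0.20 | 0.20/0.840 = 0.238 | 0.08/0.816 = 0.098 | 0.140 | 1.17 |
| 0.30 | 0.20/0.760 = 0.263 | 0.08/0.724 = 0.110 | 0.153 | 1.27 |

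At e = 0.30, the unscored share is 0.80·0.30 = 24% of control and 0.92·0.30 = 28% of experimental patients. If the delirium rates were equal in the two arms, the gap would be zero at every e. In this model early discharge enlarges a real difference but does not create one.

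**4. Patients untestable on day 5 (MoCA only)**

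Let u be the share of delirium-status patients who cannot be tested, with no early discharge. The delirious fraction among scored patients is p(1 − u)/(1 − pu).

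- u = 0.25: 0.158 − 0.061 = 0.097, ratio 0.81.
- u = 0.50: 0.111 − 0.042 = 0.069, ratio 0.58.
- u = 1: ratio 0, with 160·0.20 = 32 control and 160·0.08 ≈ 13 experimental patients unscored.

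The last line is a ceiling. The 20% and 8% count subsyndromal delirium and any episode within the five days, including episodes that have ended by day 5.

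**5. Scale in points**

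Assume a deficit of 6 MoCA points (range 4 to 8) and an SD of 5, neither of which is in the documents. The full-data difference is 6·0.12 = 0.72 (0.48 to 0.96), with standard error 5·√(2/147) = 0.58. At e = 0.10 it becomes 0.78, and at e = 0.30 it becomes 0.92. The largest of these discharge biases is 0.20 points, or 0.20/0.58 ≈ 0.3 standard errors.

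**The case against.** The strongest reply is that an article condenses a fuller protocol, and that rules for deaths, early discharge and unscorable tests commonly sit in that protocol or in the analysis plan. This stands: the absence of a scoring rule here is not a fault. It does not answer the conflict over when the tests are given, which is in the text shown and decides whether a score exists.

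A reader might go further and infer that the scores cannot be obtained, that the t-test is confined to patients alive, in hospital and testable on day 5, and that the arms are therefore selected by the primary outcome. The documents do not support this:

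- Only death makes a score impossible. Nothing says that assessment ends at discharge, and the Abstract points to testing at discharge.
- Nothing says that delirious patients are untestable. Some may complete the MoCA with a low score, which is valid data.
- Being untestable on day 5 is not the primary event but a subset of it of unknown size.
- The FIM is not shown to be lost through delirium. Its exposure is through discharge and death.
- No complete-case rule is stated, and the t-test is not the only analysis named. The adjusted regression does not by itself remove selection after randomisation.

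It is also fair to say that the assumed discharge bias is modest, that a true difference of 0.72 points is only about 1.2 standard errors even with complete data (0.72/0.58), and that the two mechanisms oppose each other.

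**Conclusion.** The point holds as a conflict over timing with a risk of selective loss. The article gives two time points for the MoCA and FIM. Under the day-5 one, patients who leave early may go unscored, and on the article's own account of delirium and stay these would mainly be patients without delirium.

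For assumed early-discharge shares of 10% to 30% of non-delirious patients, a delirium-mediated MoCA difference would be inflated to about 108% to 127%. This rests on the planned 20% and 8%, on early leavers being non-delirious and unscored, and on the software acting only through delirium. The article gives no length of stay from which to fix the shares. Loss of untestable patients acts in the opposite direction by an unknown amount, so the net direction cannot be determined. The conclusion that neither outcome could be read as an effect of the software would go too far.

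Both outcomes are secondary, and the primary analysis is not affected. The change should still be made, because scores that are not collected cannot be recovered.

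**What to change.** State one rule in both the Abstract and Outcomes: MoCA and FIM on day 5, or on the day of discharge if that comes first. For any score still missing, record the reason (discharge, death, unable to be tested because of delirium) and report the counts by arm.

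The treatment of deaths and untestable patients can be left to the analysis plan. A rank-based analysis that places them lowest is one option as a sensitivity analysis; it changes the question asked and need not become the main comparison.

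The cost is small. Assessors already see in-patients twice a day for the CAM, so the tests are brought forward for early leavers and not added. The downside is that the day of assessment varies for patients who leave early, so that day should be recorded as well.
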